### Nurses’ experience measures

Registered and enrolled nurses’ perceptions of safety attitudes, organisational readiness to change, barriers to physical assessment, staff engagement and multidisciplinary collaboration will be quantified using the following validated tools: (i) Safety Attitudes Questionnaire Short Form (Teamwork Climate and Safety Climate subscales) [63], (ii) Organisational Readiness to Change Assessment (Context Assessment subscales) [64], (iii) Barriers to Nurses’ use of Physical Assessment Scale [65], (iv) Utrecht Work Engagement Scale-17 [66], and (v) Interprofessional Collaboration Scale [67].

### Medical officer’ experience measures

Medical officers’ perceptions of safety attitudes and multidisciplinary collaboration will be measured using the following validated tools (i) Safety Attitudes Questionnaire Short Form [63] and (ii) Interprofessional Collaboration Scale [67].

## Procedure

### Patients

All patients who are present on participating wards for 48 h or longer during the pre/post intervention survey periods will be invited to participate in the patient survey. Patients will be ineligible if they are: less than 18 years old, non-English speaking, or too unwell or cognitively impaired to participate (as determined by the primary nurse or site lead). Patients will be approached a maximum of three times to participate in the survey. If present, visiting family members and carers may assist patients to complete the survey.

### Nurses

All registered and enrolled nurses (including nursing unit managers) who have worked on participating wards for two weeks or more will be invited to complete the nurse survey, including part-time, temporary contract and casual staff who work 4 shifts or more per month. Agency staff employed by an external provider and assistants in nursing will not be eligible to participate.

### Medical officers

All medical staff (i.e. interns, residents, registrars and consultants) who have been based on participating wards for 2 weeks or longer will be invited to participate in the survey.

## Data collection

### Primary outcome data

Primary outcome data of medical emergency team calls (rapid response calls and ‘Code Blue’ calls), unplanned intensive care unit admissions, in-hospital falls, hospital-acquired pressure injuries, and patient demographic data (age, sex, comorbidity information, and time on ward) will be retrieved from routinely collected hospital data. Data will be collected for the trial period and the preceding three years (i.e. January 2020 – December 2023). Where routinely collected data does not clearly identify the location where a patient experienced an outcome event, medical record chart audits may be undertaken.

### Experience measures surveys (patient, nurse, medical officer)

Prior to each step and at the conclusion of the trial, patient, nurse, and medical officer experience measures will be obtained via paper-based self-administered surveys. Surveys will be distributed to intervention ward participants by site leads or ward-level clinical champions. For patients who have vision or physical impairments, but otherwise are eligible and willing to participate, site leads or caregivers may provide assistance in completing the survey. Return of completed surveys will constitute informed consent. Surveys will also contain some brief demographic questions: patient surveys will ask time on ward, age, sex, previous admission history and the 0–100 overall health visual analogue scale from the EuroQol 5-Dimensions Questionnaire [68]; nurse and medical officer surveys will ask their position title and how long they have worked on the participating ward.

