**Methods:**

A stepped-wedge cluster randomised trial will be conducted over 52 weeks. The intervention consists of a nursing core physical assessment, structured patient-centred bedside handover and improved multidisciplinary communication and will be implemented in 24 wards across eight hospitals. The intervention will use theoretically informed implementation strategies for changing clinician behaviour, consisting of: nursing executive site engagement; a train-the-trainer model for cascading facilitation; embedded site leads; nursing unit manager leadership training; nursing and medical ward-level clinical champions; ward nurses’ education workshops; intervention tailoring; and reminders. The primary outcome will be a composite measure of medical emergency team calls (rapid response calls and ‘Code Blue’ calls), unplanned intensive care unit admissions, in-hospital falls and hospital-acquired pressure injuries; these measures individually will also form secondary outcomes. Other secondary outcomes are: i) patient-reported experience measures of receiving safe and patient-centred care, ii) nurses’ perceptions of barriers to physical assessment, readiness to change, and staff engagement, and iii) nurses’ and medical officers’ perceptions of safety culture and interprofessional collaboration. Primary outcome data will be collected for the trial duration, and secondary outcome surveys will be collected prior to each step and at trial conclusion. A cost–benefit analysis and post-trial process evaluation will also be undertaken.

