### Design

A pragmatic, hybrid type 1, stepped-wedge cluster randomised trial design will be conducted [32] with a cost–benefit analysis and qualitative process evaluation. The hybrid type 1 trial design allows the evaluation of intervention implementation concurrent to the primary clinical efficacy outcomes. Combining these data produces more useful information for decision-makers aiming to promote the more rapid translation of evidence to practice [33]. As our trial involves enhancement of current best practice, a stepped-wedge design is desirable as all participants eventually receive the intervention. The trial intervention, implementation and evaluation are informed by the Medical Research Council Framework for complex interventions [34] and evidence-based implementation strategies [35].

The trial intervention will be sequentially implemented over three periods of 17 weeks, totalling 51 weeks. A total of 24 wards will be enrolled to the trial, with eight sites each contributing three wards (Fig. 2).

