Patient, nurse and medical officer experience measures will be reported as means and standard deviations of overall component scores, and changes from pre- to post-intervention will be tested using a GLMM with a Poisson link function adjusting for respondent age, tenure (if appropriate) and correlation within ward. We will conduct secondary analyses: i) to investigate changes in outcomes over time, ii) perform the above with additional fixed effects for patient demographics (age, sex, comorbidity), and iii) model differences in primary outcome components by level of comorbidity. A statistical analysis plan pre-specifying all analyses will be formulated and finalized prior to the study data lock.

All analysis will be conducted in the R language for statistical computing, using the lme4 package for generalised linear mixed models [69].

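### The protocol does not say which wards complete the experience surveys at each round. Its wording leans toward a schedule with no concurrent control wards, and the listed survey model has no calendar-time term.

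*Protocol article*

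**What the plan says.** The section on experience measures surveys sets the timing: "Prior to each step and at the conclusion of the trial, patient, nurse, and medical officer experience measures will be obtained". The Abstract repeats it: "secondary outcome surveys will be collected prior to each step and at trial conclusion". Neither sentence names the wards covered at a given round.

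Three other statements bear on it:

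- On distribution, the same section says: "Surveys will be distributed to intervention ward participants by site leads or ward-level clinical champions".
- Under Procedure, patients present for 48 h or longer "during the pre/post intervention survey periods will be invited to participate in the patient survey".
- Under Data analysis, for the experience scores, "changes from pre- to post-intervention will be tested" with a mixed model that adjusts for respondent age, tenure where appropriate, and correlation within ward. No calendar-time term is listed. For the patient event outcomes, the same section does list fixed effects for secular trend.

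The Design section supplies the calendar and the clusters: "The trial intervention will be sequentially implemented over three periods of 17 weeks, totalling 51 weeks", and "A total of 24 wards will be enrolled to the trial, with eight sites each contributing three wards". Wards are randomised to three sequences, stratified by hospital.

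**The concern.** A stepped-wedge trial separates the intervention from calendar time because, at the middle time points, some wards have switched and others have not. Survey endpoints gain from this only if both kinds of ward are surveyed at the same round.

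The wording permits a schedule on which this never happens: a ward is surveyed before its own step and then at the end. A site lead could reasonably read it so, since the manager workshops and nurse education timed before each step concern only the wards entering that step. Every patient, nurse and medical officer experience measure would then be an uncontrolled before-after comparison against a single end-of-trial survey. Season, staffing, policy change or survey fatigue at that round would be read as intervention effect.

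The analysis plan cannot repair this afterwards. A model can gain a period term, but surveys never collected cannot be recovered. The three years of pre-trial data cover routinely collected outcomes, not surveys.

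The second part concerns the model. Even with a sound schedule, the listed covariates leave the pre/post contrast exposed to drift over time.

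**Working it through.** **Inputs from the protocol.** 24 wards; three sequences; three periods of 17 weeks. Rounds fall at about weeks 0, 17, 34 and 51.

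**Assumptions, not document figures for surveys.** 8 wards per sequence (one per hospital; Fig. 2 is not shown). Base case: 15 responses per ward-round, ICC 0.05, cluster autocorrelation (CAC) 0.8, scores in SD units. Second set: 20 responses, ICC 0.03 to 0.08 (the range the protocol gives for event outcomes, borrowed here), ward intercept only (CAC 1). The protocol states no sample size or precision for the surveys, so there is no figure to reproduce.

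**Schedules compared**

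| Schedule | Wards at rounds 1, 2, 3, 4 | Ward-rounds | Rounds with both switched and unswitched wards |
|---|---|---|---|
| A: own pre-step round plus end | 8, 8, 8, 24 | 48 | none |
| Minimum: about to step plus already stepped | 8, 16, 24, 24 | 72 | 2 and 3 |
| B: all wards every round | 24, 24, 24, 24 | 96 | 2 and 3 |

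**Identifiability under A.** Let θ be the intervention effect and τ1 to τ4 the round effects. The expected within-ward changes are:

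- sequence 1: θ + τ4 − τ1
- sequence 2: θ + τ4 − τ2
- sequence 3: θ + τ4 − τ3

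θ and τ4 always appear together, so only their sum can be estimated. The design matrix (intercept, effect, three round terms) has rank 4 of 5, or 27 of 28 with fixed ward effects.

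**Linear trend under A.** With drift d per period the changes are θ + 3d, θ + 2d and θ + d. θ is now identified (rank 3 of 3) because the gaps differ. A shift f confined to the final round adds f to all three changes, leaves the slope unchanged, and moves the estimate from θ to θ + f.

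**No time term under A.** The mean pre-to-end gap is (51 + 34 + 17)/3 = 34 weeks, or two periods, so the bias is 2d.

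**No time term under B.** Generalised least squares gives a bias of 1.89d to 1.95d over ICC 0.03 to 0.08 with 20 responses. Surveying more wards does not by itself remove it.

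**What that does to the test.** Take a true effect of zero, d = 0.05 SD per 17 weeks and 20 responses.

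- A: SE = √(2 × (1 − ICC)/20/24), which at ICC 0.05 is √(2 × 0.95/20/24) = 0.063. The bias is 0.10, so the false-positive rate is 35 to 37% over the ICC range.
- B: SE is 0.047 to 0.048 and the bias 0.095 to 0.098, so the rate is 51 to 54%. It is higher because the SE is smaller around a similar bias.

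**Standard errors with time in the model**

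| Schedule and time term | Base case | 20 responses, ICC 0.03 to 0.08 |
|---|---|---|
| A, categorical round | not estimable | not estimable |
| A, linear trend | 0.176 | 0.144 to 0.150 |
| Minimum, categorical round | 0.102 | not shown |
| B, categorical round | 0.096 | 0.079 to 0.080 |

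In the second set, assuming a linear trend under A raises the SE from 0.062–0.064 to 0.144–0.150, about 2.3 to 2.4 times. Under the minimum schedule and B, the effect is estimable with full round effects (rank 5 of 5), and a final-round shift then contributes no bias.

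**The case against.** The strongest objection is that no sentence states the one-pre, one-end schedule. A reader might infer that each ward is definitely surveyed only twice; the document does not support that.

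- The timing sentences describe four calendar rounds without restricting wards, and all three respondent groups are defined on participating wards.
- Every ward eventually receives the intervention, so an intervention ward may simply mean a trial ward.
- The pre/post phrase also describes incident rates, which are collected continuously, so it names a contrast rather than a schedule.
- Where the authors mean only the wards in a step, as for the manager workshop, they say so.
- Figs. 1 and 2 are not shown and may settle the matter.

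All of this stands. The schedule part is therefore a finding of ambiguous wording that leans one way, not of a fixed design error.

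A reader might also infer that, on schedule A, the effect can never be separated from time. That is too strong: a linear trend identifies it, although the answer then rests wholly on that assumption.

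Finally, extra surveys alone cure little, and an analysis plan not shown may include a time term. The first half is right, and the fix below covers both parts. On the second, the article lists the survey covariates and includes time only for the event outcomes, so the stated model should be corrected. A later plan cannot supply the missing concurrent surveys.

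**Conclusion.** The point holds in two parts and concerns secondary endpoints only.

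1. **Schedule.** The protocol does not fix which wards are surveyed at each round, and its wording permits and leans toward schedule A. On that schedule the effect is fully aliased with survey round. It is recoverable only through an assumed parametric trend, at an SE of 0.176 SD in the base case against 0.096 to 0.102 SD for the schedules with concurrent controls.
2. **Model.** With the covariates as listed, drift biases the pre/post contrast by about 1.9 to 2.0 times the drift per 17-week period, under either reading of the schedule.

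The rank results and the one-for-one transfer of a final-round shift follow from the layout and need no assumed variances. The SEs and false-positive rates depend on assumed responses, ICC, autocorrelation and drift. The ranking of schedules is the same at 10 and 25 responses per ward-round. Confidence that schedule A is intended is only medium.

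**What to change.** In the section on experience measures surveys, state that each of the four rounds covers at least the wards about to step and every ward that has already stepped, or else all 24 wards. Replace the reference to intervention ward participants with wording that matches the choice. In the survey model under Data analysis, add a categorical survey-round effect. Both changes are needed.

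**Cost.** The minimum version adds 72 − 48 = 24 ward-rounds to schedule A (8 at round 2 and 16 at round 3). That is three per hospital if each hospital has one ward per sequence. All 24 wards adds 96 − 48 = 48, for a modest further gain (SE 0.102 to 0.096 SD in the base case). The downside is more paper surveys across three respondent groups, more respondent burden and possible survey fatigue. If all wards at every round is already intended, the cost is one clarifying sentence and one model term.

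If the survey schedule cannot be extended, describe the experience results as uncontrolled before-after comparisons.

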### Core physical assessment

All registered and enrolled nurses will be required to conduct a comprehensive and systematic physical assessment for their allocated patients at the beginning of each shift. This consists of 16 core physical elements structured in the ‘A-E’ format (Table 1) [38, 39]. After this initial assessment, nurses will continue to perform vital sign monitoring per hospital policies and patient requirements.

**Table 1 Tab1:** Core physical assessment elements, structured in A-E format [39]

A-E	Assessment Elements
Airway	1. Assess airway patency
Breathing	2. Measure respiratory rate 3. Evaluate work of breathing 4. Measure oxygen saturation
Circulation	5. Palpate pulse rate and rhythm 6. Measure blood pressure by auscultation 7. Assess urine output
Disability	8. Assess level of consciousness 9. Evaluate speech 10. Assess for pain
Exposure	11. Measure body temperature 12. Inspect skin integrity 13. Inspect and palpate skin for signs of pressure injury 14. Observe any wounds, dressings or drains, invasive lines 15. Observe ability to transfer and mobilise 16. Assess bowel movements

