**Fig. 3 Fig3:**
[figure not shown]
Cascading facilitation flowchart

Each participating hospital will nominate an internal nursing staff member to act as the site lead responsible for implementing the trial at their local site. Site leads will be nurses in an existing higher-grade position or senior clinical nurses who have high influence amongst the nursing discipline, with experience in nurse education and facilitating clinical practice change. Responsibilities will include: (i) engaging with nursing and medical management teams and presenting trial overviews, (ii) delivering nurses’ education workshops and additional top-up training as required, and (iii) supporting nursing unit managers to iteratively co-design their ward action plan with the ward clinicians to implement and embed the intervention.

A one and a half-day in-person train-the-trainer workshop with the site leads will be conducted two months prior to the start of the trial. Site leads will be briefed on the overall trial design, the intervention components, and their role within the trial, in particular, proposed engagement processes and training for delivering the nurses’ education workshops. The research team will remotely provide training, support, and resources for site leads to deliver the intervention and engage with site-specific stakeholders. Resources will include the workshop teaching material (PowerPoint presentation, demonstrative videos, and learning handouts), action plan templates, posters and lanyard cards to use as reminders on the ward, and intervention guides for optional internal audits.

Prior to and during the trial, all site leads will meet fortnightly with the research team via videoconference as a learning collaborative group to share progress, report risks, and discuss strategies for navigating barriers. Determined per site, regular internal meetings will be organised by the site lead to maintain engagement and support nursing unit managers (e.g., weekly to fortnightly action plan meetings with nursing unit managers and monthly progress reports with directors of nursing).

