### Ward nurses’ education workshops

A fortnight prior to the commencement of each step, site leads will conduct a two-hour workshop for nurses on the participating ward. The workshop will be repeated over five consecutive days to maximise attendance, with additional education sessions as required. These workshops will cover the three intervention components and facilitate discussion around anticipated ward-specific factors, specifically enablers, barriers, and proposed solutions.

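### Site leads, who implement the intervention and know whether a ward has stepped, may help impaired patients complete the patient safety and experience surveys, which opens these secondary outcomes to social-desirability bias

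*Protocol article*

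**What the plan says.** The patient-reported secondary outcomes are the Patient Measure of Safety Questionnaire and the Friends and Family Test (Outcome measures, Patients' experience measures). They are collected on paper before each step and at the end of the trial. Self-completion is the default.

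The article assigns these tasks:

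- **Invitation.** Everyone on the ward for at least 48 hours "during the pre/post intervention survey periods will be invited to participate in the patient survey" (Procedure, Patients). In addition, "Patients will be approached a maximum of three times to participate in the survey".
- **Screening.** One exclusion is a matter of judgement: "too unwell or cognitively impaired to participate (as determined by the primary nurse or site lead").
- **Distribution.** "Surveys will be distributed to intervention ward participants by site leads or ward-level clinical champions" (Data collection, Experience measures surveys).
- **Help with completion.** For patients whose vision or physical impairment is the obstacle, "site leads or caregivers may provide assistance in completing the survey". The Patients section separately lets visiting family and carers assist.

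The site lead's role is set out under the train-the-trainer model. Each hospital nominates a nurse to "act as the site lead responsible for implementing the trial at their local site". Under Ward nurses' education workshops, a fortnight before each step, "site leads will conduct a two-hour workshop for nurses on the participating ward".

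**The concern.** A survey of perceived safety should record the patient's own view. Here a senior nurse in charge of the programme may sit with an inpatient who cannot read or mark the form alone, and help that patient rate the ward where the programme runs. Patients in that position tend to soften criticism. The helper also knows whether the ward is before or after its step, and has a reason to hope for better scores after it.

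The survey analysis compares pre-intervention with post-intervention scores (Data analysis). A change in how often site leads help, or in how strongly their presence colours the answers, would enter that comparison as if it were an effect of the intervention.

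These two instruments are the only patient-reported outcomes listed, and patient-centred bedside handover is one of the three intervention components. The Conclusion expects to speak to patient experience if the trial succeeds. A credible patient-reported result is therefore worth protecting.

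**Working it through.** The article states no sample size, response rate, exclusion rate, assistance rate or target difference for the patient survey, so there is no figure to reproduce. The check sets the sections side by side and then sizes the selection route on stated assumptions.

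**1. Does the helper have a stake and know the ward's status?** Yes. The site lead is responsible for local implementation and runs the nurse workshops just before each step, so knows when each ward crosses over.

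**2. How could assistance bias the effect?** Let *a* be the proportion of returned surveys completed with a site lead's help, and *d* the mean shift in score, in SD, that this help causes. The bias in the pre-to-post change is

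*a*(post) × *d*(post) − *a*(pre) × *d*(pre).

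It is zero if both quantities stay the same. It is positive if help becomes more frequent, or its influence stronger, after the step. The article gives neither *a* nor *d*, so no number can be put on it.

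**3. Could the stated adjustment remove it?** The survey model adjusts for respondent age, tenure where appropriate and correlation within ward, and secondary analyses add patient demographics. None of these describes who helped, so none corrects an answer altered by the helper.

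**4. How large is the selection route?** The primary nurse may also make the fitness judgement. Ward nurses deliver the intervention (Core physical assessment: "All registered and enrolled nurses will be required to conduct a comprehensive and systematic physical assessment for their allocated patients"), so that judgement is not independent either. Assume a normally distributed score and exclusion of the lowest fraction *p* on a variable correlated *r* with the score. The mean among those remaining rises by

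*r* × φ(z_p) / (1 − *p*), in SD.

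The factor φ(z_p)/(1 − *p*) is:

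| *p* | φ(z_p) | φ(z_p)/(1 − *p*) |
|---|---|---|
| 0.10 | 0.1755 | 0.1950 |
| 0.12 | 0.2000 | 0.2273 |
| 0.15 | 0.2332 | 0.2743 |

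The exclusion rule applies before and after the step, so only the difference between periods biases the effect:

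| Excluded before → after | Difference in factor | *r* = 0.3 | *r* = 0.5 |
|---|---|---|---|
| 10% → 10% | 0 | 0 | 0 |
| 10% → 12% | 0.0323 | 0.010 SD | 0.016 SD |
| 10% → 15% | 0.0793 | 0.024 SD | 0.040 SD |

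The percentages and correlations are assumptions. On them, the selection bias is about 0.01–0.04 SD.

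**The case against.** The strongest defence is that the arrangement is narrow and symmetrical. All patients on the ward for 48 hours or longer are to be invited, with up to three approaches. Judgement enters through one criterion only, and leaving fitness to take part to someone who knows the patient is ordinary practice. Site-lead help is confined to vision or physical impairment, with caregivers as the alternative. The same roles act in both periods, so a constant influence cancels from the pre-to-post change and mainly affects generalisability. Embedded site leads are also a deliberate response to restricted access and to the researcher-intensive feasibility study. All of this stands. It limits the size of the problem but does not give a reason for the person implementing the trial to help with the form when carers are already allowed to.

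Four stronger readings are tempting, and the article does not support them:

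- *Staff choose who may answer the survey.* A reader might infer this, but the age, language and 48-hour criteria are not left to the nurse or site lead.
- *Gatekeeping could raise post-intervention scores by 0.06–0.18 SD.* Excluding 10% gives 0.06–0.10 SD, and excluding 20% gives 0.105–0.175 SD (factor 0.350 × *r* of 0.3–0.5). Both require that nobody is excluded before the step, whereas the rule applies in both periods.
- *The group subject to discretion is large.* No rate is given.
- *Exclusions and assistance go unrecorded.* The form and any screening log are not shown, and a condensed article commonly leaves such details to the full protocol.

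The process evaluation does require interviewers who are not involved in delivering the intervention. That shows the authors value such separation, but interviews are a different method from paper surveys, so it is not a contradiction.

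**Conclusion.** The concern holds in a limited form. Allowing site leads to help complete the patient surveys is a stated and avoidable weakness. It opens two secondary outcomes to social-desirability bias if the help or its influence differs before and after the step. Such a difference is plausible but not shown, and its size cannot be derived from the article.

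Selection through the fitness judgement is the lesser risk: about 0.01–0.04 SD if exclusions rise from an assumed 10% to 12–15% at an assumed correlation of 0.3–0.5, and nil if the rates and their link with the score are equal.

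The primary composite comes from routinely collected hospital data and is not touched. Nor is the cost–benefit analysis, which values the effect on that composite. This is a cheap improvement worth making, not a threat to the trial's main conclusion.

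**What to change.** 1. In Data collection, Experience measures surveys, delete site leads as helpers. Limit help to family or carers, who are already allowed, or to existing staff who neither deliver nor facilitate the intervention.
2. Add one tick-box to the patient form: completed alone, or helped and by whom (if the form does not already have it).
3. Repeat the patient-survey analysis on unassisted surveys only, as a sensitivity analysis.
4. Report the number of patients excluded as too unwell or cognitively impaired, separately for the pre- and post-intervention periods. The criterion itself can stay as it is. The counts show whether it was applied evenly.

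The cost is a change of wording, one item on the form and a simple count, which means slightly more paperwork. A few impaired patients with no carer or neutral helper may be lost from the survey. No new staff are needed, because a neutral helper is used only where one already exists.
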